### 3.4. Exclusion Criteria

Dysphagia caused by head injury or neurological disease other than strokePatients who suffered from recurrent stroke (not the first-time stroke)Unstable cardiac arrhythmiaLife-threatening infectionUnconsciousness or severe cognition deficitsOral or throat diseases that display dysphagiaPatients with bleeding tendencies or thrombocytopenia, who are taking anticoagulants or have advanced malignancyPatients with tracheostomy

### 3.5. Withdrawal Criteria

Participant's decision to drop out from study at any time for any reasonNoncompliance with the treatment protocolOccurrence of any unexpected serious side effects

## 4. Blinding

Throughout the whole study process, the outcome assessor will be kept blind. As this is a single-blind controlled designed study, it is unfeasible to keep the patient and acupuncturist blind. The primary outcome measure will be carried out by registered speech therapist hired by the project. They will not be informed any information about the patient allocation and will be instructed to keep minimum interaction with patients during the whole study.

## 5. Intervention

Patients in both acupuncture and no-acupuncture control group will receive the conventional supportive and rehabilitative treatment, such as swallowing therapy programmes, nonoral feeding, medications, and physical stimulation [8, 9]. On top of the supportive treatment, patients in the acupuncture group will receive real acupuncture treatment, while patients assigned to the control group will receive no-acupuncture treatment during the study. Baseline assessment will be conducted for all eligible participants. The participants who agree to accept acupuncture treatment will be allocated to treatment group, while those who refuse to accept acupuncture treatment will be allocated to control arm.

All acupuncture treatment sessions will be performed by two to three acupuncturists who are registered Chinese Medicine Practitioners in Hong Kong and have at least 3 years of clinical experience in acupuncture practice. Interventions will be conducted according to STRICTA and ICH-GCP guidelines. To ensure the consistency of skill of various acupuncturists, two to three training workshops will be provided to acupuncturists who have participated in the study prior to the commerce of the study. The acupuncture experts panel of School of Chinese Medicine, The Chinese University of Hong Kong, will provide technique training on the selection of acupuncture points and needling techniques. The workshops will be videotaped for education purpose.

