## Abstract

*Background. *Dysphagia is one of the most common complications of stroke. Acupuncture is widely employed to treat poststroke dysphagia in East Asia. No evidence is established to support such treatment approach. This proposed study aims to evaluate the effectiveness and safety of acupuncture for the treatment of poststroke dysphagia.* Methods and Design.* This is a multicenter, pragmatic, single-blinded, nonrandomized controlled clinical trial. A total of 140 eligible patients will be enrolled in the study. Subjects who are eligible in study but refuse to have acupuncture treatment will be put on the no-acupuncture control arm. Both groups of patients will receive standard routine care, while the patients of intervention group will receive add-on standardized acupuncture treatment. Each participant in intervention group will receive a total of 24 sessions of acupuncture treatment (three times per week). The primary outcome measure is the Royal Brisbane Hospital Outcome Measure for Swallowing (RBHOMS). Secondary outcome measures include functional oral intake scale, swallow quality-of-life questionnaire in Chinese version, BMI of the participant, and adverse events. All outcome measures will be assessed at baseline, at the end of acupuncture treatment (month 2), and at two months after treatment (month 4).* Ethics and Dissemination.* The ethics approval of clinical research study was granted by the Research Ethics Committee of both New Territories East and West Cluster of Hong Kong. Written informed consent will be obtained from all participants and the study will be undertaken according to the ICH-GCP Guidelines.* Trial Registration.* This trial is registered with chictr.org (registration number: ChiCTR-TRC-12002621 and registration date: 2012-10-26).

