## 7. Manipulation Procedure

Sterile disposable stainless steel needles of various lengths and diameters will be used in the study. The standardized needling manipulation methods on different acupuncture points are described as follows: GB12, GB20 (a depth of 0.8–1.2 cun with the needle tip pointing towards the throat will be punctured, and needles will be rotated with reinforcing techniques); CV23 (about 1.0 cun towards the root of the tongue will be inserted obliquely, and mild lifting and thrusting technique will be applied for about 1 min); DU20 (at an angle of 30 degrees, angle to a depth of 0.5 to 0.8 cun will be inserted obliquely, and the needle will be rotated about 30 seconds before withdrawing the needle); LI4 (puncture perpendicularly for 0.5 to 1.0 cun, and apply for 30 seconds reinforcing technique with the lifting and thrusting movement); HT5 (a depth of 0.5 cun will be punctured perpendicularly, reinforcing technique with the lifting and thrusting movement will be applied for 30 seconds); Hangsang (a needle of 75 mm in length will be applied to prick the posterior wall of the throat at the depth of about 0.15 cun for 4 times without retaining the needle); Shanglianquan (a depth of 1.0–1.5 cun towards the root of the tongue will be inserted obliquely, and mild lifting and thrusting technique will be applied for 30 seconds); Lower 2/5 of the motor zone of scalp acupuncture (the needle will be inserted transversely at an angle of 15 degrees to the skin surface and push the needle to about 1.0 cun in depth, and twirling method will be applied for about 30 seconds); ST40 (the needle will be punctured perpendicularly for 1.5 cun, and reducing technique by lifting and thrusting the needle will be applied); LR3 (the needle will be inserted perpendicularly for 0.5–1.0 cun, and reducing techniques by lifting and thrusting the needle for 30 seconds will be applied) (Table 1).

The acupuncture treatment will be administered once every two days, three times a week, and the whole treatment period will last for 2 months. A total of 24 acupuncture treatment sessions will be carried out on each patient.

Participants who are allocated to nonacupuncture controlled group will receive routine care without acupuncture treatment.

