Blinding is a crucial measure to assure the quality of the trial. All outcome assessor and statistician will be kept blind throughout the whole process. We will minimize the interaction between the patients and outcome assessors. Neither the RBHOMS assessor nor the staff who administer the questionnaire knows the group allocation of the participants.

One main limitation of this study is lack of randomization. Randomization is a key procedure to minimize the selection bias and ensure the comparability of all parameters between the intervention group and control group. However, concerning the timeframe and budget of our pilot study, nonrandomization approach will be utilized. To reduce the selection bias of our study, subjects will be recruited from different sources, including hospitals, speech therapy outpatient clinics, and Chinese medicine clinics. Moreover, all the prognostic factors and baseline characteristics of participants such as gender, age, occupation, life style, and onset time of stroke will be controlled in both acupuncture group and nonacupuncture control group. All data will be collected to examine the baseline comparability and explore the possible sources of dissimilarity and make proper statistical adjustment later.

As for all clinical trials, subject recruitment is one of the most critical factors for the trial's successful implementation. In our study, various venues and approaches will be utilized to augment the subject recruitment process. Free Chinese medicine consultation will be provided to control arm participants as an incentive. In addition, we will also hold promotional talks in the Chinese medicine clinics to facilitate the recruitment process. Moreover, we may also place advertisements on local newspapers and contact the stroke patients association to boost subject recruitment if recruitments from hospitals and Chinese medicine clinics turn out to be undesirable.

Nonetheless, most of potential subjects of this study are stroke sufferers. They always have other complications, such as immobility. In order to reduce the dropout rate and to enhance the compliance of patients, some treatment sessions may be conducted at affiliated mobile clinics.

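### The add-on comparison takes background care as common to both arms, but self-selected arms, mixed recruitment sources and an unadjusted primary test let unequal swallowing therapy pass as an acupuncture effect

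*Protocol article*

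**What the plan says.** The Abstract defines the contrast: "Both groups of patients will receive standard routine care, while the patients of intervention group will receive add-on standardized acupuncture treatment". Section 5 (Intervention) repeats it: "Patients in both acupuncture and no-acupuncture control group will receive the conventional supportive and rehabilitative treatment". An open list of examples follows: swallowing therapy, nonoral feeding, medications and physical stimulation. No minimum amount and no provider is given. Section 7 (Manipulation Procedure) describes the control arm: "Participants who are allocated to nonacupuncture controlled group will receive routine care without acupuncture treatment".

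Sections 3.1 and 5 allocate by preference: those who accept acupuncture form one arm, those who refuse it form the other. On recruitment, section 12 (Discussion) says "subjects will be recruited from different sources, including hospitals, speech therapy outpatient clinics, and Chinese medicine clinics". It adds a fallback if those sources yield too few: "we may also place advertisements on local newspapers and contact the stroke patients association to boost subject recruitment". Section 3.2 (Subject Recruitment) lists the Chinese medicine centres and three hospital speech therapy clinics, and says that suitable patients are referred by hospital speech therapists.

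Section 11 (Data Analysis) names a chi-square test for the primary outcome and an exploratory multivariable analysis of baseline data. Section 12 promises statistical adjustment later. Its examples of factors are gender, age, occupation, life style and time of stroke onset. It also offers control participants a free Chinese medicine consultation as an incentive.

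**The concern.** In a randomised trial, variable usual care is harmless to validity because it balances on average. Here nothing balances it. If people reached through Chinese medicine clinics accept acupuncture more often, and are less often in a swallowing programme than people reached through speech therapy, then recruitment source is tied to both arm and background therapy. The opposite is also conceivable: acceptors may be the patients who seek more treatment of every kind. Either way, the difference in the proportion at stage D would combine acupuncture with unequal swallowing therapy, and the trial's question about the added effect of acupuncture would not be answered cleanly. Section 12 offers the mixture of sources as a way to reduce selection bias. With self-selected arms, mixing sources can instead add to it unless source enters the analysis.

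**Working it through.** **1. Does the text leave the route open?**

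- Common care is asserted (Abstract, section 5), but its content is illustrative and its provider unstated.
- The arms follow patient choice (sections 3.1 and 5).
- Recruitment is partly outside speech therapy (sections 3.2 and 12).
- No criterion in section 3.3 or 3.4 requires current swallowing therapy.
- The stated primary test has no covariates (section 11).
- The factors named for control (section 12) include neither therapy nor source.

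These together mean that an imbalance, if it arises, goes straight into the primary result.

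**2. The plan's own figure, used only for scale.** Section 10 gives 60 per arm for a 20-point difference in stage D, 80% power and 5% error; section 11 makes tests two-sided. No control proportion is printed, so 60 cannot be reproduced uniquely. Without continuity correction, 8% vs 28% needs 57 per arm and 10% vs 30% needs 62. The present point does not depend on this figure.

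**3. Size, on assumed inputs.** The documents give neither the effect of swallowing therapy on stage D nor its uptake by arm. Assume an effect of 10 to 20 points and a between-arm gap in uptake of 20 to 40 points.

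Bias = gap in uptake × therapy effect

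| Gap | Effect | Bias | Share of the 20-point target |
|---|---|---|---|
| 0.20 | 0.10 | 0.02 | 10% |
| 0.40 | 0.10 | 0.04 | 20% |
| 0.20 | 0.20 | 0.04 | 20% |
| 0.40 | 0.20 | 0.08 | 40% |

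**4. Consequence for the chi-square at 60 per arm.** Further assumptions: stage D without therapy is 10% or 30%, and uptake is centred on 50%.

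*No acupuncture effect.* The two-sided rejection rate is Φ((d − 1.96·se0)/se1) + Φ((−d − 1.96·se0)/se1), where d is the bias, se0 the pooled and se1 the unpooled standard error.

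- Largest bias, 10% base: the arms are 0.10 + 0.20 × 0.30 = 0.16 and 0.10 + 0.20 × 0.70 = 0.24. The rejection rate is 19.4% instead of 5%. With a 30% base (0.36 vs 0.44) it is 14.5%.
- Smallest bias: 0.14 vs 0.16 gives 6.1%, and 0.34 vs 0.36 gives 5.6%.

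*True 20-point effect, acupuncture arm with less therapy, largest bias.* The expected difference is 0.20 − 0.08 = 0.12.

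- 10% base: 0.24 vs 0.36 has power 29.8%, against 67.0% with equal uptake (0.20 vs 0.40).
- 30% base: 0.44 vs 0.56 has power 25.8%, against 59.3% (0.40 vs 0.60).

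*True 20-point effect, acupuncture arm with more therapy, largest bias.* The expected difference is 0.20 + 0.08 = 0.28, so the effect is overstated.

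**5. Chinese medicine contact.** Section 7 describes control care as routine care without acupuncture. Section 12 gives the same participants a free Chinese medicine consultation. A consultation is not necessarily acupuncture, so the two need not conflict, but its timing and content are not stated. The acupuncture arm has 24 sessions with Chinese Medicine Practitioners. Whether the consultation falls inside the comparison period must be settled and the passages reconciled.

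**The case against.** A reader might infer that the trial does not supply the conventional care. No passage says so. Section 4 says "The primary outcome measure will be carried out by registered speech therapist hired by the project", which gives the project's therapists an assessor role, and the term routine care suggests existing services, but that is inference. The supportable statement is that no provider is named.

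A reader might also picture many participants outside swallowing care. Section 3.2 gives speech-therapist referral as a route, section 3.3 requires a modified diet because of dysphagia, and newspapers and the association are only a fallback. This narrows the likely gap. It does not close it: Chinese medicine clinics remain listed as sources, and a modified diet is not a swallowing programme.

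The list of factors in section 12 is illustrative, and adjustment is promised. That stands, so it would be wrong to say that adjustment is absent. But it is left for later and unspecified, while the named primary test is unadjusted.

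Usual care is a legitimate comparator in a pragmatic trial, the lack of randomisation is openly acknowledged, and detail on concomitant treatment may sit in the full protocol. Accordingly, the absence of session counts from a condensed article is not held against the plan. What remains is what the article itself fixes: preference allocation, mixed sources and an unadjusted primary test, beside a claim of common care.

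**Conclusion.** The point holds as a weakness of design and analysis that should be corrected; it is not a demonstrated bias. The plan allows background swallowing therapy to differ by arm and gives the primary test no means of removing the difference. The 2 to 8 points, and the error rates and power that follow from them, rest wholly on assumed therapy effects, uptake gaps and base rates. They show that a plausible imbalance could matter against a 20-point target, and no more. The direction is unknown. That acceptors of acupuncture come more often from Chinese medicine clinics is plausible but not stated.

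**What to change.** 1. Record two baseline items for every participant: in a swallowing-therapy programme (yes/no), and recruitment source.
2. Make the primary stage D comparison a logistic regression on arm, adjusted for these two items and the other prespecified baseline prognostic factors. Keep the chi-square as the unadjusted supporting result. Tabulate arm by source first: if nearly everyone from one source is in one arm, the model cannot separate the two, and the report should say so.
3. Report swallowing therapy and Chinese medicine consultation by arm. Therapy received after entry is best described rather than adjusted for, since acupuncture may influence it.
4. Reconcile sections 7 and 12 on the control arm's consultation, and section 3.2 with section 12 on whether all participants come through speech-therapist referral.
5. Word the conclusion as acupuncture added to the care actually received.

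The cost is one extra baseline item, a note of source and a slightly larger model. The covariate list should stay short: at 10% vs 30% with 60 per arm there would be only 6 + 18 = 24 participants at stage D. No new eligibility restriction is needed; requiring registration with a speech therapy service would narrow a pragmatic trial without showing that therapy is received. Adjustment covers only what is measured, so the limits of a non-randomised comparison remain.

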## 6. Treatment Principle and Acupuncture Point Selection

Based on TCM theory, the pathogenesis of dysphagia after stroke is due to the insufficiency of the liver and kidney, the stagnant qi and blood that fail to nourish the tongue, and pathogenic factors, notably wind and phlegm, that further obstruct the meridians and the throat, resulting in swallowing difficulty. The participants will be further classified into two subtype patterns by registered Chinese Medicine Practitioner involved in the study, that is, (1) pathogenic wind phlegm syndrome and (2) liver yang rebellion syndrome. Those patients with dizziness and thin tongue coating belong to the liver yang rebellion syndrome, while those who are with greasy tongue coating belong to the pathogenic wind phlegm syndrome. All patients in acupuncture group will receive acupuncture at acupuncture points such as GB12 (Wan Gu, bilateral), GB20 (Feng Chi, bilateral), CV23 (Lian Quan), DU20 (Bai Hui), and LI4 (He Gu, bilateral) and HT5 (Tong Li, bilateral), Hangsang, Shanglianquan, and Lower 2/5 of the motor zone of scalp acupuncture.

Besides the above regular acupuncture points, additional acupuncture points will be used for patients' clinical syndrome subtypes. These additional points include ST40 (Fenglong, bilateral) for pathogenic wind phlegm subtype and LR3 (Taichong, bilateral) for liver yang rebellion type.

## 7. Manipulation Procedure

Sterile disposable stainless steel needles of various lengths and diameters will be used in the study. The standardized needling manipulation methods on different acupuncture points are described as follows: GB12, GB20 (a depth of 0.8–1.2 cun with the needle tip pointing towards the throat will be punctured, and needles will be rotated with reinforcing techniques); CV23 (about 1.0 cun towards the root of the tongue will be inserted obliquely, and mild lifting and thrusting technique will be applied for about 1 min); DU20 (at an angle of 30 degrees, angle to a depth of 0.5 to 0.8 cun will be inserted obliquely, and the needle will be rotated about 30 seconds before withdrawing the needle); LI4 (puncture perpendicularly for 0.5 to 1.0 cun, and apply for 30 seconds reinforcing technique with the lifting and thrusting movement); HT5 (a depth of 0.5 cun will be punctured perpendicularly, reinforcing technique with the lifting and thrusting movement will be applied for 30 seconds); Hangsang (a needle of 75 mm in length will be applied to prick the posterior wall of the throat at the depth of about 0.15 cun for 4 times without retaining the needle); Shanglianquan (a depth of 1.0–1.5 cun towards the root of the tongue will be inserted obliquely, and mild lifting and thrusting technique will be applied for 30 seconds); Lower 2/5 of the motor zone of scalp acupuncture (the needle will be inserted transversely at an angle of 15 degrees to the skin surface and push the needle to about 1.0 cun in depth, and twirling method will be applied for about 30 seconds); ST40 (the needle will be punctured perpendicularly for 1.5 cun, and reducing technique by lifting and thrusting the needle will be applied); LR3 (the needle will be inserted perpendicularly for 0.5–1.0 cun, and reducing techniques by lifting and thrusting the needle for 30 seconds will be applied) (Table 1).

The acupuncture treatment will be administered once every two days, three times a week, and the whole treatment period will last for 2 months. A total of 24 acupuncture treatment sessions will be carried out on each patient.

Participants who are allocated to nonacupuncture controlled group will receive routine care without acupuncture treatment.

## 8. Primary Outcome

Royal Brisbane Hospital Outcome Measure for Swallowing (RBHOMS) is a valid bedside scale for monitoring difficulties in daily swallowing function based on clinical indicators of swallowing, but not on texture-modified diets [20]. RBHOMS is a 10-point ordinal scale that ranges over four stages of oral intake: stage A, nil by mouth (levels 1–3); stage B, commencing oral intake (level 4); stage C, establishing oral intake (levels 5–7), and stage D, maintaining oral (levels 8–10). Both acupuncture group and nonacupuncture control group patient will be conducted three times RBHOMS, with one being conducted at baseline, one at the end of treatment (2 months after inclusion), and the last one at the end of follow-up period (2 months after treatment completion). All RBHOMS will be conducted by a registered speech therapist blinded to group allocation.

## 9. Secondary Outcomes

The secondary outcome measures include functional oral intake scale [21], swallow quality-of-life questionnaire in Chinese version [22], BMI [7], and adverse event report.

Functional oral intake scale, or known as swallow function scores, is a 7-point scale that describes the severity of swallowing dysfunction.

Swallow quality-of-life questionnaire in Chinese version consists of 12 items. The items covered all physical and psychosocial impact of the patients. Swallow quality-of-life questionnaire in Chinese version is chosen as secondary outcome because it is as sensitive, valid, and reliable as original version [22].

All adverse events as defined by the Ethics Committee will be fully recorded on the Adverse Event Page of the Case Report Form.

All functional oral intake scale, swallow quality-of-life questionnaire in Chinese version, and BMI will be assessed at baseline (before the intervention), the end of treatment (2 months after inclusion), and the end of follow-up period (2 months after treatment completion).

